## Abstract

**Background:**

Impaired dexterity of the weaker upper extremity is common post stroke and it is recommended that these individuals practice many repetitions of movement to regain function. However, stroke rehabilitation methods do not achieve the required intensity to be effective. Touchscreen tablet technology may be used as a motivating tool for self-training impaired dexterity of the weaker upper extremity post stroke.

**Methods/Design:**

Rehab-let is a self-training protocol utilizing game apps on a touchscreen for practicing movement of the weaker upper extremity. We will conduct a pilot randomized controlled trial to assess Rehab-let compared to traditional self-training to improve dexterity of the weaker hand, and to increase self-training time and satisfaction in individuals with subacute stroke. Forty individuals with stroke undergoing subacute rehabilitation will be randomly allocated to Rehab-let or a traditional self-training program using therapeutic aids such as balls, blocks and pegs. All participants will be requested to perform self-training for 60 minutes a day, 5 times a week for 4 weeks. Dexterity assessed by The Nine Hole Peg Test is the main outcome measure. Assessments will be administered pre and post the self-training intervention by assessors blind to the group allocation.

**Discussion:**

The outcomes of this study will inform the design of a fully powered randomized controlled trial to evaluate the effectiveness of Rehab-let. If found to be effective, Rehab-let can be used during subacute rehabilitation to increase treatment intensity and improve dexterity. Potentially, Rehab-let can also be used after discharge and might be ideal for individuals with mild stroke who are often not referred to formal rehabilitation.

**Trial Registration:**

Current Controlled Trials NCT02136433 registered on 17 September 2014.

## Background

Weakness of the upper extremity is common post stroke, and a large population of individuals is left with a non-functional hand following their stroke [1, 2]. These Individuals need to practice many repetitions of movement at high intensity for efficient motor learning and neural plasticity to occur [3, 4]. However, despite the evidence, stroke rehabilitation does not achieve the required intensity [5–7]. Self-directed training, where the client practices the movements individually, is one way to increase training time and the number of repetitions. Individuals performing self-directed upper extremity exercises and activities, for an additional 30 minutes per day for 1 month during in-patient stroke rehabilitation, improved their functional ability and daily use of their weaker upper extremity compared to individuals who did not perform upper extremity self-directed training [8].

Games such as cards, pegs and blocks are commonly used in clinical practice to improve hand skills and potentially can be used for self-training. However, these traditional treatment methods are often boring and not motivating [9] and thus do not encourage intensive self-training in the clinic or at home. Moreover, with traditional therapeutic tools it is difficult to train speed of motion and reaction time and almost impossible to objectively quantify performance for precise and objective evaluation and as well as for monitoring improvement.

In the past decade commercial interactive video-games (e.g., EyeToy, Wii, Xbox Kinect) have been utilized by clinicians to motivate their clients in order to increase training time and promote health [10]. Despite the fact that video-games were not specifically developed for rehabilitation, they have been used in stroke rehabilitation to improve the function of the weaker upper extremity [11, 12] and to increase the repetition of purposeful movements [13]. However, video-games mainly encourage shoulder and elbow movements or gross hand movements, but not specifically dexterity (i.e., the ability to use the fingers in a coordinated and rapid manner). Dexterity is often impaired after stroke [14], and hinders the ability to use the weaker upper extremity for daily activities [15] such as eating or grooming.

Recent developments in touchscreen tablet technology may have the potential to fill this gap and serve as a self-training tool for finger dexterity [16]. These ubiquitous and portable computing devices with a web connection have a user interface that is built around a multi-touch screen. The hardware capabilities of these tablets include an accelerometer and a gyroscope that measure acceleration and orientation [17]. Application software, also known as an application or an app, is a computer software designed to help the user perform singular or multiple related specific tasks or games when using these devices. The user swipes, taps or pinches the screen with their fingers to perform game-like activities, which is more naturalistic than operating a mouse or using a computer keyboard. Many of the apps include gaming and music factors that appear to make a major contribution towards enhancing enjoyment and motivation. These factors have been found to facilitate participation in regular exercise [18].

Tablets have been recently used in pilot studies in rehabilitation. The iPad (Apple Inc., Cupertino, CA, USA) was perceived as a helpful tool for enhancing engagement in therapeutic activities and socialization [18] and found to have potential use for hand rehabilitation of individuals with stroke [19]. These preliminary findings support the potential use of tablets for stroke rehabilitation and the need for further research [18]. There are many health-related apps for tablets (e.g., to promote physical activity, monitor salt intake, weight loss); however, commercially available apps for rehabilitation of impaired dexterity are scarce and some of them are not released for public use. For example, Saposnik et al. [20] are currently examining their newly developed Stroke Rehab® game app for home-based rehabilitation poststroke. Countless game apps, which can be downloaded from the App Store (Apple Inc., Cupertino, CA, USA) or Google Market (Google, Mountain View, CA, USA), have been developed for the healthy general population. Despite the fact that they encourage finger and hand movement while playing fun games, only a limited number of apps might be successfully played by individuals with motor impairments due to stroke. Whereas the development of apps specifically for rehabilitation is warranted, it is unknown if existing tablet apps, that are accessible to everyone, can be used by individuals recovering from stroke with a mild to moderate motor upper extremity impairment. More so, due to the tablet's unique characteristics, it is unknown if playing these apps would result in improved dexterity, increased self-training time and higher client satisfaction compared to traditional directed self-training. We therefore propose a pilot randomized controlled trial (RCT) to compare the effectiveness of Rehab-let, a self-training protocol utilizing tablet technology with existing apps, to a traditional self-training program to improve impaired dexterity of individuals with stroke [8]. Individuals during subacute stroke rehabilitation will be targeted first since they receive on-going professional supervision. We hypothesize that using touchscreen tablets with existing, appropriately selected apps (Rehab-let), will result in improved dexterity, increased self-training time and high satisfaction in individuals with stroke as compared to the control group. These preliminary findings will assist with planning a future fully powered RCT.

### Trial design

A pilot single-blind randomized controlled study with assessments pre and post the intervention. Participants will be randomized by block randomization using an allocation ratio of 1:1 to receive self-training either by Rehab-let using the tablet or by performing traditional activities/exercises. All participants will perform the self-training in addition to the standard rehabilitation care.

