### Implementation of the intervention

Individuals will be approached during their first week in rehabilitation and their written consent will be obtained. Following the first assessment, individuals will be randomly allocated to receive self-training either by Rehab-let (experimental group) or GRASP (control group). Concealed allocation will be maintained. A single session will be provided to each participant by an occupational therapist (OT) to teach them how to play the apps (experimental) and perform the exercises (control). Each participant will also receive a booklet with explanations and photographs of the self-training apps/exercises and a log sheet. Participants will be requested to fill in a dailylog regarding their training time. In addition, participants will be asked to indicate whether they have had assistance or someone present during the self-training. Participants will be instructed to play the apps (experimental)/perform the exercises (control) with their weaker upper extremity for a total of 60 minutes a day for 5 days over a 1-month period. The 60 minutes can be divided into 2 or 3 daily sessions. The OT will monitor the participants weekly to assure training is been performed daily, to verify logs are filled in accurately, to adapt the level of the apps/exercises if needed, and to assure that there are no adverse effects. Participants will be given the OT's phone number and will be encouraged to contact him/her during the week, if needed. Participants randomized to the Rehab-let self-training will be taught how to play 4–5 different apps on the tablet, selected together with the OT from a pool of 20 apps. These apps will be available for them in a folder on the iPad’s screen. See Table 2 for a summary of the study’s interventions.

**Table 2 Tab2:** Description of study interventions based on the intervention description and replication (TIDieR) template [38]

Brief name	Rehab-let
Why	Increasing treatment intensity can improve the impaired dexterity of the weaker upper extremity however there is insufficient training time for the weak upper extremity during subacute stroke rehabilitation
What	a. Existing iPad Apps (from the Apple Store (Apple Inc., Cupertino, CA, USA)) using the Rehab-let protocol (experimental), traditional treatment aids such as blocks, pegs and a towel using the GRASP protocol (control)

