#### Outcome measures

The primary outcome measure is improved dexterity, which will be assessed by The Nine Hole Peg Test (NHPT) [23]. This test is a valid and reliable test to assess dexterity in individuals with stroke [24] and the time to insert and remove 9 pegs is measured. The following secondary outcome measures will be used; grip and pinch strength [25] will be assessed by the Jamar and pinch dynamometer. The Fugl-Meyer Motor Assessment [26] will assess the motor impairment of the upper extremity. The Action Research Arm Test [27] will assess the functional ability of the upper extremity by grasping and moving objects of different size and weight. The Visual Analogue Scale [28], which quantifies the perceived level of pain intensity on a scale of 0–10 cm, will also be used. Self-training time will be used to assess adherence to the self-training protocol and will be taken from the daily logs. Satisfaction from the self-training program will be determined by a Satisfaction Questionnaire, developed for the study. The questionnaire will query the participant's satisfaction with the self-training intervention and his or her perceived benefit of the intervention to improve upper extremity’s function. Responses will be rated on a scale of 1–5. The System Usability Scale [29] will be filled in by individuals in the Rehab-let group – to assess their subjective usability of the tablet for rehabilitation. Each of the 10 items is rated on a 5-point scale from 1 (disagree totally) to 5 (agree totally), an overall score is calculated ranging from 10 (low usability) to 100 (high usability) points. Demographic and stroke characteristics will also be collected at baseline as well as information regarding prior tablet experience. In addition, independence in basic activities of daily living of this population will be characterized using the Functional Independence Measure [30].

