#### Study samples

A total of forty participants will be recruited for this pilot study: 20 randomized to the Rehab-let self-training protocol (experimental group) and 20 to the GRASP self-directed training (control group). These results will be sufficient to calculate the effect size to use in sample size power calculations for a larger RCT.

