### Data analysis plan

All data will be inputted in IBM SPSS statistics software, version 21 (Armonk, NY, USA). Descriptive statistics for the study population and outcome measures will be computed for both groups to verify that groups are similar preintervention. A repeated measures analysis of variance (ANOVA) will be used to compare the NHPT scores within and between groups; with repeated measures for time (pre intervention versus post intervention) between the groups (Rehab-let versus GRASP) and for interaction effect between time and group. A difference above 32.8 seconds [31] on the NHPT for the weaker upper extremity will be considered to be a clinically meaningful change. Differences in the upper extremity secondary measures as well as adherence (self-training time) and satisfaction will be compared as well. Intention-to-treat analysis will be conducted with the last observation carried forward method.

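### No baseline severity term in the between-arm Nine Hole Peg Test comparison, although allocation is by 1:1 blocks with no stratum described and severity is measured before allocation

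*Protocol article*

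**What the plan says.** **Allocation.** The Trial design section states: "Participants will be randomized by block randomization using an allocation ratio of 1:1". It names no block size and no stratification factor. Study samples gives the numbers: "A total of forty participants will be recruited for this pilot study: 20 randomized to the Rehab-let self-training protocol", with 20 in the control arm.

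**Timing.** Implementation of the intervention states: "Following the first assessment, individuals will be randomly allocated to receive self-training". Baseline NHPT and the other clinical measures are therefore known before each allocation. One of them is the Fugl-Meyer, which "will assess the motor impairment of the upper extremity".

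**Entry.** The Population section asks for some finger movement and full hand function before the stroke, but sets no bound on a motor score. The Background speaks of "individuals recovering from stroke with a mild to moderate motor upper extremity impairment", but this is not an inclusion criterion.

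**Outcome and analysis.** For the NHPT, "the time to insert and remove 9 pegs is measured". The Data analysis plan states: "A repeated measures analysis of variance (ANOVA) will be used to compare the NHPT scores within and between groups", with terms for time, group and their interaction. No covariate is named. Descriptive statistics are computed "to verify that groups are similar preintervention", and no consequence is given if the groups are not similar.

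**The concern.** Blocks keep the numbers per arm equal but do nothing for case mix. With two time points, the group-by-time test is a comparison of mean change between arms. A constant baseline difference cancels in that comparison, but a difference in how much people can change does not.

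The article gives reason to expect such a difference. A time in seconds cannot fall by more than its starting value, and the plan's threshold for meaningful change is 32.8 s. A participant who starts below 32.8 s cannot improve by that much, while a slow performer can. If severe participants change more, a chance surplus of them in one arm moves the observed contrast.

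The stake is the trial's stated purpose. Study samples says the results will supply the effect size for sizing a larger trial, and that estimate would carry noise that data already collected could remove.

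**Working it through.** The article gives no alpha, power, SD or target effect, so there is no stated figure to reproduce beyond N = 40.

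**Inputs from the article:** 40 participants, 20 per arm; 1:1 blocks; two assessments; threshold 32.8 s.

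**Assumed, because the article gives none:** number of severe participants K = 12, 16 or 20 of 40; severe-minus-mild gap in mean NHPT improvement D = 0 to 60 s; SD of change 25 s (severe) and 10 s (mild).

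**Step 1. Chance of imbalance.** The number of severe cases x in one arm is hypergeometric (K severe among 40, 20 drawn). The difference between arms is d = 2x − K.

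| K | P(\|d\| ≥ 4) | P(\|d\| ≥ 6) |
|---|---|---|
| 12 | 30.1% | 8.2% |
| 16 | 33.3% | 10.5% |
| 20 | 34.3% | 11.3% |

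Permuted blocks of 4 (assumed size) do not alter this: simulation gives 34.5% for K = 20.

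**Step 2. Shift in the change contrast, with no treatment effect.** Shift = (d/20) × D. For K = 16, the mean of |d| given |d| ≥ 4 is 4.79, so the mean shift is 4.79/20 × D = 0.239 × D. This is 1.2 s for D = 5, 2.4 s for D = 10, 4.8 s for D = 20, 9.6 s for D = 40 and 14.4 s for D = 60.

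A version with a continuous severity score gives a similarly wide range. One standard error of the standardised baseline difference is √(2/20) = 0.316. The shift is 0.316 × baseline SD × slope of change on baseline. It runs from 0.3 s (SD 10 s, slope 0.1) to 9.5 s (SD 60 s, slope 0.5).

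**Step 3. Precision, K = 16.** The within-severity variance of change is 0.4 × 25² + 0.6 × 10² = 310, which contributes (2/20) × 310 = 31 to the variance of the contrast. The variance of d/20 is 4 × (20 × 0.4 × 0.6 × 20/39)/400 = 0.0246. So unadjusted SE = √(31 + 0.0246 × D²). The adjusted SE is from simulation with allocation unchanged and a two-level severity factor in the model.

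| D (s) | SE unadjusted (s) | SE adjusted (s) |
|---|---|---|
| 0 | 5.6 | 5.6 |
| 10 | 5.8 | 5.6 |
| 20 | 6.4 | 5.6 |
| 40 | 8.4 | 5.6 |
| 60 | 10.9 | 5.6 |

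Stratified allocation also gave about 5.6 s for D = 20, 40 and 60, so the analysis term alone recovers essentially all the precision.

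**Step 4. Error rate.** In 20,000 simulated trials (K = 20, D = 20 s, residual SD 25 s, no treatment effect), the unadjusted comparison rejected in 5.1% overall. Among trials with |d| ≥ 4 it rejected in 7.4%, against 5.0% with adjustment for severity.

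**Step 5. Is linear adjustment for baseline NHPT enough?** With assumed baselines of 110 s (SD 30) for severe and 40 s (SD 10) for mild participants, the shift remaining given |d| ≥ 4 was 1.1, 2.3 and 3.3 s for D = 20, 40 and 60. That removes most of the shift but not all of it.

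**The case against.** Unstratified blocks are a legitimate design for a 40-person pilot, and nothing in the Trial design section is an error. Chance imbalance is already part of the standard error, and the overall type I error is kept. Both points stand.

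The gain also depends on quantities that the article does not give. At a 10 s gap, adjustment takes the SE only from 5.8 to 5.6 s, and at a zero gap it gains nothing. That stands too. It limits the size of the point but does not argue against adjusting, because adjustment costs almost nothing when the gap is small.

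The article is a condensed text. Its silence on strata does not show that allocation ignores severity, and a fuller protocol may name factors. This stands for allocation. It carries less weight for the analysis, since the Data analysis plan sets out the terms of the primary model and severity is not among them.

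A reader might infer that in about one trial in three the NHPT contrast will be wrong by several seconds. The one-in-three figure concerns the severity split and holds for the assumed severe shares. The seconds come wholly from assumed gaps and SDs. A reader might also infer that programme effect and case mix could not be told apart. Baseline characteristics are to be described by group, and baseline scores are available for adjustment.

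**Conclusion.** The point holds as a matter of precision and of the estimate given an observed imbalance, not of validity. As described, neither allocation nor analysis uses a severity measure that is in hand before allocation. If 30% to 50% of the 40 are severe, a difference of 4 or more severe cases between arms has a probability of about 30% to 34%.

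Its effect on the NHPT contrast cannot be stated from the article. Under assumed improvement gaps of 5 to 60 s, the mean shift given such an imbalance is about 1 to 14 s. The unadjusted SE is 6.4 to 10.9 s for gaps of 20 to 60 s, against about 5.6 s adjusted. These figures rest on the assumed severe share (16 of 40) and SDs of change (25 and 10 s).

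The documents do not support calling this bias or an inflated overall error rate, nor do they show that the allocation scheme must be redrawn.

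**What to change.** In the Data analysis plan, state that the between-arm NHPT comparison adjusts, for all 40 participants, for baseline severity taken from the first assessment. This can be a two-level severity factor, baseline NHPT, or both. Fix the cut for the factor before unblinding, and place those unable to finish the baseline NHPT in the slower level. The factor is worth having alongside baseline NHPT because a linear term alone may leave some shift.

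The cost is one or two degrees of freedom. No visit, measurement or participant is added, and there is no material loss if severity turns out not to predict change. The cut must be justified by the sponsor, since the article supplies no value.

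Stratifying or minimising the remaining allocations by the same factor is optional. Recruitment is under way and the number already allocated is not stated, so the added benefit may be small. It would need an amendment and a new concealed list, and could leave arm sizes slightly unequal. If the full protocol already names strata, one sentence in the article would say so, and the same factor should enter the model.

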## Methods

### Population

For individuals with stroke undergoing subacute in-patient rehabilitation to be eligible for this study, must comply with all of the following inclusion criteria:Provision of written informed consent prior to entry into the studyAge above 20 yearsAt least 1 week post strokeEvidence of ischemic or hemorrhagic stroke confirmed by computed tomography (CT) or magnetic resonance imaging (MRI) head scanFull function of the hand prior to strokeAbility to partially move their fingersCognitively intact or mild impairment (as assessed by a score above 20 on the Mini Mental State Examination [21])

Exclusion criteria: other neurological conditions besides stroke, uncontrolled seizures and acute orthopedic conditions of the upper extremity.

### Interventions

#### Rehab-let

A self-training protocol utilizing the Apple iPad touchscreen tablet (Apple Inc., Cupertino, CA, USA) with a variety of game-like apps will be used. We selected apps that encourage finger movement, could be motivating for adults, are not restricted in time and are not too fast. See Table 1 for examples of apps to be used.

**Table 1 Tab1:** Examples of apps for self-training of experimental group

Name of app, developer, link	Screenshot	Description and aim
Dexteria BinaryLabs, Inc. http://goo.gl/b6rGE		Each finger needs to touch colored shapes in a timely manner/trace letters/pinch crabs walking on the screen. Encourages finger dexterity and isolation of movements, and provides a performance report. It was developed specifically for training fine motor skills, but not purposefully for stroke
FastTouch Pedro Riera http://goo.gl/6yfZlq		Finger tapping as many times as possible in a pre-fixed time period. Encourages speed of movement and can be performed with one or more fingers
Scribble Kid Mile 26 Studios http://goo.gl/OdwDce		Tracing and drawing on the tablet with fingers or with a stylus. Encourages accuracy and qualitative movement of the hand
Fruit Ninja Halfbrick Studios http://goo.gl/TkaAS		Cutting (swiping) fruit that appear in different locations on the screen, in increased frequency while avoiding other shapes. Encourages eye-hand coordination, reaction time and accuracy. Recommend to play "Arcade" mode within a time frame

